Create and Connect	8–17	These workshops are one-day programs that offer opportunities for participants to connect with peers in a safe, creative space. Various workshops are offered including music and song writing, photography and visual art such as graffiti and meme-making, plus other art and craft-based activities. Participants learn how to use music, photography, and art to express themselves, in an environment where they have the opportunity to connect with other young people who have a family member living with mental health challenges. The workshop allows participants to explore their personal and shared experiences through open dialogue and develop inclusive communication skills, including both visual and spoken language.
Satellite Connect in person or online	18–25	A structured peer support and peer development program that gives young people the space to be heard, learn new skills, and share their stories. Also covered is how their lived experience might be used to positively shape and influence the lives of younger children. Online versions of Satellite Connect run for 6 weeks, while in-person editions of Satellite Connect takes place across 3 weeks. During the program, participants meet other young people who have a family member living with mental health challenges, and interact, collaborate, and form connections with others living with similar families. Various themes are discussed including self-care and self-compassion, communicating creatively, talking about mental health, mental illness, language and stigma, and considering next steps for participants to practice newly acquired skills.

These programs were selected because they provide a good overview of participants’ ages and represent the capstone programs offered to young carers. Given they attract the most participants, this focus also provides rich data for analysis. The SROI covers the period of January 2023 through to June/July, 2024 with the final evaluation report to be delivered in August 2024.

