## Evidencing outcomes and giving them a value

### Evidencing outcomes

This stage involves finding data that demonstrates whether preferred outcomes have occurred and then valuing those outcomes. A convergent parallel mixed method approach will be employed, consisting of qualitative and quantitative data collection and analysis and then comparing and relating the two before interpreting them (34).

All participants will be asked demographic questions about their age, gender identity, cultural background, language spoken at home and the nature of their family member’s illness. They will also be asked which Satellite program/s they have been involved in.

For the quantitative component of the evaluation, a within-subject pre-post study design will be used to identify potential changes over time (35). Accordingly, participants (and their parents, for children aged 18 years and under) in targeted programs will be invited to participate in questionnaires on program entry, and then 6 months later, using the number of programs as a covariate (as some will attend multiple programs). Participants are asked to record a nickname when completing questionnaires, to ensure traceability across time one and two (pre and post). Individual and longitudinal conversations will also be employed. Further detail for these steps is presented below.

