### Duration and drop off

Duration refers to how long an outcome lasts for, while drop off acknowledges that outcomes may continue to last for many years but may decrease over time, or if it is sustained, may be influenced by other factors. To calculate drop off, we will deduct a fixed percentage from the remaining level of outcome at the end of 6 months. This decision will be based on the longitudinal interviews, which follow young people over the course of the project, including those who have maintained a relationship with Satellite and those who have not.

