## Calculating the SROI

Calculating the SROI involves adding up the outcomes (value), applying the discounts (attribution, displacement, deadweight and drop off) and comparing the result to the investment or costs incurred in delivering the program. Costs involved for Satellite involve employing staff to facilitate programs (including administration and registration), insurance, venue hire, catering, materials and travel (Satellite sometimes pays for transport so that young people/children can attend programs). Expenses associated with reimbursing YAC members for their input and advice on the programs offered is also included. Our analysis spanned a six -month period only (as indicated in Table 3), which does not necessitate the use of a discount rate to account for the time value of money (58). As the timeframe is less than a year, no additional adjustments for the differing value of money over time were required.

Once the net present value of costs and outcomes have been established (taking into consideration drop off, deadweight and displacement), the final ratio can be calculated. The formula for calculating the return on investment is:

SROI ratio = Social value of stakeholder outcomes (discounted)

Cost of providing programs

According to Arvidson et al. (23), an SROI ratio greater than one indicates a positive return on investment, or in other words, where the benefits of the investment are greater than its costs. The calculation is based on proxy values, as outlined in Table 3.

As the results are influenced by non-quantitative variables and assumptions, a sensitivity analysis for the SROI will be calculated to promote robustness. After establishing a base case scenario as outlined above, each key assumption will be changed (by ±10%), one at a time, to ascertain how much the SROI ratio changes. Changes in the SROI will be compared for each variation and those assumptions that cause the most significant changes in the SROI ratio identified. Several plausible scenarios will be developed including best case, worse case and moderate scenarios, using most optimistic to most pessimistic values of each of the assumptions. Each of these scenarios will be reported including a discussion of which assumptions have the most significant impact on the SROI ratio.

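### Drop-off is defined on the outcome remaining after six months, yet it is deducted from a benefit counted for six months only

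*Protocol article*

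**What the plan says.** Four statements in the protocol article bear on the time base of the ratio.

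- **Horizon.** Under Calculating the SROI: "Our analysis spanned a six -month period only (as indicated in Table 3), which does not necessitate the use of a discount rate". The reason follows: "As the timeframe is less than a year, no additional adjustments for the differing value of money over time were required". The value column of Table 3 is headed as covering a six-month period.
- **Drop-off.** Under Duration and drop off: "we will deduct a fixed percentage from the remaining level of outcome at the end of 6 months". The percentage is not given; it is to be informed by the longitudinal interviews.
- **Use in the ratio.** The calculation sums the outcome values, then proceeds by "applying the discounts (attribution, displacement, deadweight and drop off) and comparing the result to the investment or costs incurred in delivering the program". Drop-off is named again when the article describes the net values that enter the final ratio.
- **Window and follow-up.** Under Establishing scope and identifying stakeholders: "The SROI covers the period of January 2023 through to June/July, 2024 with the final evaluation report to be delivered in August 2024". Under Evidencing outcomes, participants "will be invited to participate in questionnaires on program entry, and then 6 months later". The denominator is given as "Cost of providing programs", with a list of cost items but no stated period.

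**The concern.** Drop-off describes how an outcome fades in the periods after the one first valued. If only one six-month period is valued, no later value exists for it to reduce. If later value is meant to count, the six-month limit is not true, Table 3 lacks the later value, and the reason given for omitting a discount rate has to be looked at again. The article holds both positions.

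The SROI ratio is the summary result. The article reads a ratio above one as a positive return and foresees the findings being used to seek funding. An analyst who follows the text literally removes value that, by the article's own definition, has not yet faded. Another who gives drop-off its usual role adds a second period. Their base cases would differ substantially.

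**Working it through.** **Inputs from Table 3 (per person, six months).** Connectedness $21,861.38; resilience $4,200; hope $1,250. The drop-off percentage d is not in the article, so 10%, 25% and 50% are assumed for illustration.

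**Reproducing the article's figures.**
- Hope: 2,500 / 2 = 1,250. Reproduced.
- Resilience: 14 × 300 = 4,200. Reproduced, though this is the price of a course of sessions and has no time base of its own.
- Connectedness: 42,818.76 / 2 = 21,409.38, against 21,861.38 printed. The difference is $452.00, about 2.1%. This is a separate matter. The printed figure is used below, and the proportional effect of drop-off does not depend on it.
- Sum: 21,861.38 + 4,200 + 1,250 = $27,311.38.

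**Reading A: drop-off taken from the only period valued.** Numerator = V × (1 − d), before the other deductions.

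**Reading B: drop-off applied to a second six-month period.** Numerator = V + V × (1 − d), with the first period intact.

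| Assumed d | No drop-off, six months | Reading A | Reading B (12 months) | B / A |
|---|---|---|---|---|
| 10% | $27,311 | $24,580 | $51,892 | 1.90 / 0.90 = 2.1 |
| 25% | $27,311 | $20,484 | $47,795 | 1.75 / 0.75 = 2.3 |
| 50% | $27,311 | $13,656 | $40,967 | 1.50 / 0.50 = 3.0 |

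**Effect on the ratio.** If the deductions multiply, the others cancel in the comparison and the cost is unchanged, so Reading A lowers the ratio by exactly d%. At d = 25%, any ratio between 1 and 1 / 0.75 = 1.33 without drop-off would be reported as below one.

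**Does the planned sensitivity analysis cover this?** Varying an assumed 25% by ±10% gives 22.5% to 27.5%. Reading A then gives 27,311.38 × 0.775 = $21,166 to 27,311.38 × 0.725 = $19,801. Neither the no-drop-off value of $27,311 nor the 12-month value of $47,795 lies in that range. The variation changes the size of the assumption, not the structure of the base case.

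**Calendar.** January 2023 to June/July 2024 is 18 to 19 months. A participant has a six-month outcome inside the window if entry was by the end of December 2023 or January 2024. No last-entry date is given. The share without such an outcome is 0% if entry closed by then, and 6/19 = 32% to 6/18 = 33% if entry ran evenly to the end.

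**The case against.** The best defence is that the drop-off sentence can be read as a cautious downward adjustment to the level counted at six months, in keeping with the SROI principle of not overclaiming. The percentage is left open, to be informed by interviews that include young people who have disengaged, and best, worst and moderate scenarios are planned. It stands that the deduction errs on the low side and that scenario reporting would make some of its effect visible. It does not remove the inconsistency. The follow-up questionnaire falls at six months, so fading up to that date should already show in the measured outcome. A further deduction for what remains then is a deduction for later time.

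A reader might also infer that numerator and denominator do not match: that late entrants add cost but cannot supply a six-month outcome, or that 18 to 19 months of one side is set against six months of the other. The article does not support this. It states neither a cost period nor a last-entry date. Six months can be a horizon per participant and January 2023 to June/July 2024 a project window. A six-month benefit summed over everyone served, divided by the cost of serving them, is coherent. The study is also declared a forecast SROI, which can project outcomes not yet observed. The one-third share needs even entry to the last day. A threefold error needs a pairing of costs and participants that no section proposes. Cost-allocation detail may also properly sit in a fuller document.

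**Conclusion.** The drop-off rule is wrong as written. An analysis limited to six months of value cannot also deduct decay defined on what remains when those six months end. Followed literally, the rule lowers the ratio by the full drop-off percentage. The percentage is unknown. On assumed values of 10% to 50%, the Table 3 sum falls from $27,311 to between $24,580 and $13,656 per person, before the other deductions. This rests on the printed Table 3 values, on all three outcomes being counted for a person, and on deductions that multiply.

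The relation between the six-month horizon and the 18 to 19 month window needs a clarifying sentence and no more. A mismatch of costs and benefits is not demonstrated, and there is no ground for restricting the analysis to participants with observed six-month outcomes.

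**What to change.** State one benefit horizon in the calculation section and carry it through the drop-off section.

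- **Base case:** six months of benefit per participant, no drop-off, no discount rate.
- **Labelled scenario, if benefit beyond six months is to be counted:** state its duration, apply drop-off to the later periods only, say what the percentage rests on, and revisit discounting if the horizon exceeds one year.
- **Clarification in the same wording:** six months is the horizon per participant, and the costs are those of serving the participants whose benefits are counted within January 2023 to June/July 2024.

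The cost is a change of wording and a little more analysis; no new data are needed. The downside is that the base case loses a conservative deduction, which should be said when the ratio is reported.

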#### Giving outcomes a value

In the final part of this process, we give the identified outcomes a monetary value using financial proxies that reflect that importance of the outcome to stakeholders (see Table 3). In consultation with the YAC, a sense of connectedness and sense of belonging was considered similar to having friends. Powedthavee (64) identified the economic value of making and having new friends, in addition to existing friends, and this value was subsequently updated and converted to Australian dollars (See Table 3). Given that the original value was calculated in 2007, we adjusted it for inflation to reflect its current purchasing power, ensuring consistency with contemporary economic conditions. Although using a currency converter may not be the ideal method, this approach, when combined with inflation adjustments, provides a reasonable approximation of the value in today’s terms.

**Table 3 tab3:** SROI stage 3 outcomes.

Stakeholder		Stage 3				
Satellite young person participants		The outcomes (what changes)				
	Outcome	How will we know if the outcome has occurred	Source	How can you value the change?	Value $AUD for six-month period	Source
		Measured how?	Where this information comes from	What proxy is used to value the change?	Value of the change	Where this information comes from
	Sense of belonging and increased connectedness	Feel more connected to other young people living in similar circumstances	SDQ: Prosocial behaviour subscale (child and parent versions) LSAC items on connectedness Interviews with children/youth	Powdthavee (64) identified the economic value of friends (in addition to existing friends): 15,500 pounds per year in 2007 is equivalent to 23,903.38 pounds in 2022, converted to 2022 AUD 42,818.76 *per annum*	$21,861.38	Powdthavee (64).
		Reduced feelings of isolation and increased feelings of belonging				
	Increased resilience	Decreased mental health crises	CYRM-R total score KCS, completed by children aged 10 years and under; CASQ, completed by older children, adolescents and young adults Interviews with children/youth	The Australian Psychological Society (APS) recommends $300 per hour per child/young person for psychological services – 14 sessions	$4,200 per child/young person	APS website: https://psychology.org.au/psychology/about-psychology/what-it-costs

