	Sense of hope, optimism and possibility	Increased hope for the future that results in planning for future activities/goals, agency	Children’s Hope Scale Interviews with children/youth	Cost of a mentor such as what might be available from the Big Brothers, Big Sisters mentoring program: $2,500 per person for 12 months	$1,250	Big Brother, Big Sisters of Australia Annual Report 2019–2020 BBBS_Annual_Report_2019-2020.pdf (bigbrothersbigsisters.org.au)

We also identified a financial proxy for resilience. For the young people involved in these programs, resilience refers to achieving positive outcomes (inclusive of wellbeing) despite coming from challenging backgrounds, and adaptively coping with current stressors (see Figure 1, Theory of Change). According to Olsson et al. (48), promoting resilience at an individual level involves developing personal coping skills and resources, both of which they suggest may be obtained from one to one therapy. Pascual-Leone et al. (49) suggested 14 individual sessions is appropriate for individuals with existing issues. It was on this basis that resilience was valued as 14 individual, psychotherapeutic sessions (see Table 3). The assumption that 14 individual psychotherapeutic sessions has a similar effect to a one-day workshop (e.g., the Create and Connect program) is admittedly contestable. However, a one-day workshop that focuses on creativity and connectedness can offer an intensive, immersive experience that might be considered similar to the impact of multiple counselling sessions (33, 50). Moreover, the unique therapeutic mechanisms of creative programs can lead to profound insights and emotional processing (51–53), potentially achieving in 1 day what might take multiple counselling sessions. The added dimension of group dynamics in these programs which emphasises peer support, can amplify the overall therapeutic impact (33, 50, 51), again potentially contributing to outcomes comparable to multiple individual counselling sessions.

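### The one-way sensitivity step changes every assumption by the same ±10%, so it ranks them by arithmetic weight and not by how uncertain they are

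*Protocol article*

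**What the plan says.** The section Calculating the SROI builds the ratio by "adding up the outcomes (value), applying the discounts (attribution, displacement, deadweight and drop off) and comparing the result to the investment or costs". It then plans two layers of sensitivity analysis.

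- **One-way step.** From a base case, "each key assumption will be changed (by ±10%), one at a time, to ascertain how much the SROI ratio changes". The variations are compared and "those assumptions that cause the most significant changes in the SROI ratio identified".
- **Scenarios.** "Several plausible scenarios will be developed including best case, worse case and moderate scenarios"; these are to span the range from the most favourable to the least favourable value of every assumption. The article adds: "Each of these scenarios will be reported including a discussion of which assumptions have the most significant impact on the SROI ratio". It gives no numerical end points for these scenarios.

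Table 3 fixes the three six-month proxies: AUD 21,861.38 for connectedness (the friendship value), AUD 4,200 for resilience (14 sessions at AUD 300) and AUD 1,250 for hope. In Giving outcomes a value, the authors say that equating the 14 sessions with a one-day workshop "is admittedly contestable". Both there and under Limitations they concede that updating a 2007 friendship value by inflation and a currency converter is imperfect. Deadweight, displacement, attribution and drop-off are still to be estimated, and no programme cost is given.

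**The concern.** A one-way sensitivity analysis should tell the reader which doubts could change the conclusion. That needs two things for each input: how strongly the ratio responds to it, and how far it could plausibly be from its base value. A common ±10% supplies only the first. An input known almost exactly and an input that is little more than a guess get the same band, and the comparison then reports which has the larger coefficient.

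The plan nevertheless uses this comparison to name the influential assumptions. The article treats a ratio above one as a positive return, shares results with funders and through a public video, and expects that they may be used in lobbying. A disputed input that shows a 1.5% effect in the one-way table could be set aside as unimportant, when the small figure reflects only the narrow band chosen.

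**Working it through.** **Inputs.** The proxies are those of Table 3: F = 21,861.38, P = 4,200, H = 1,250. The article states no sensitivity result to reproduce, so I checked the proxies first.

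- Resilience: 14 × 300 = 4,200. Agrees.
- Hope: 2,500 / 2 = 1,250. Agrees.
- Connectedness: Table 3 gives the annual value as "converted to 2022 AUD 42,818.76". Half of that is 21,409.38, not 21,861.38. The difference is 452.00, or 2.1%. The two entries need reconciling, but the results below hardly change (last step).

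**Form of the ratio.** R = [sum of valueᵢ × achieved changeᵢ × (1 − deductions)] / cost. The multiplicative use of the deductions is my reading of the article's description.

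**Effect of ±10% on a proxy.** The change in R is 10% × the proxy's share of the numerator. With equal achieved change and equal deductions, the total is 21,861.38 + 4,200 + 1,250 = 27,311.38.

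| Proxy | Share | Effect of ±10% on R |
|---|---|---|
| Friendship | 80.0% | 8.0% |
| Resilience | 15.4% | 1.5% |
| Hope | 4.6% | 0.5% |

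**Effect of ±10% on a deduction d applied to all outcomes.** The change is 10% × d/(1 − d).

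| d | 0.1 | 0.2 | 0.3 | 0.5 | 0.7 |
|---|---|---|---|---|---|
| Effect on R | 1.1% | 2.5% | 4.3% | 10% | 23% |

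**Effect of ±10% on cost.** 1/1.1 − 1 = −9.1% and 1/0.9 − 1 = +11.1%.

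None of these expressions contains any measure of how uncertain the input is.

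**What the ±10% band covers, against wider illustrations.** The article gives no plausible ranges, so the wider values here are assumptions.

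- Resilience: 14 × 0.9 = 12.6 and 14 × 1.1 = 15.4 sessions, an effect of 1.5%. At 7 sessions, (2,100 − 4,200)/27,311.38 = −7.7%. At 3 sessions, (900 − 4,200)/27,311.38 = −12.1%. At 1 session, (300 − 4,200)/27,311.38 = −14.3%.
- Friendship: ±10% gives 8.0%. At half the stated value, −0.5 × 80.0% = −40%. At a quarter, −60%.

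**How far the ranking depends on data.** With assumed achieved fractions of 0.1, 0.6 and 0.6 for connectedness, resilience and hope, the weighted values are 2,186, 2,520 and 750, total 5,456. The ±10% effects become 4.0%, 4.6% and 1.4%, and resilience ranks first. With equal achieved change, a common deduction overtakes friendship's 8.0% once d/(1 − d) exceeds 0.8, that is, above about d = 0.45.

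**Using 21,409.38 instead.** Shares are 79.7%, 15.6% and 4.7%. The order is unchanged.

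**The case against.** The strongest reply is that ±10% is only one of two layers. The scenarios run from the most optimistic to the most pessimistic values, and all of them will be reported. A reader might infer from the narrow band that a fragile ratio will be passed to funders as stable. The article does not support that: if the inputs are very uncertain, the gap between the worst and best cases should show it. What the scenarios do not do, as described, is take one assumption at a time over its own range and rank it. The discussion of influence that accompanies them has no stated method other than the ±10% comparison.

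A reader might also infer that the ranking is settled before any data, with friendship first by construction. That does not hold either. The 80/15/5 split needs equal achieved change as well as equal deductions, and the deductions have yet to be estimated. Unequal change, or a deduction above about 45%, can reorder the list.

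It is fair to add that on the illustrative ranges above friendship still leads resilience (40% against 14.3%), so ±10% need not misorder the proxies. What it does misstate is the size of each effect, and therefore the position of each proxy relative to the deductions and cost.

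It is tempting to attach numerical intervals to deadweight and drop-off as well. I have not done so. The article's retest correlation of 0.64 belongs to the SDQ prosocial subscale over 12 months, not to the LSAC items, and drop-off is a fixed percentage judged from interviews.

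Finally, an article may leave scenario end points to a fuller plan. That is accepted; the point rests on the ±10% rule, which the article does fix.

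**Conclusion.** The concern holds for the one-way step. A uniform ±10% ranks assumptions by their arithmetic weight, whatever their uncertainty, while the plan uses it to say which assumptions matter most. Under equal achieved change and equal deductions it shows 1.5% for the contestable resilience proxy, where a single session would give 14.3%, and 8% for friendship, where halving would give 40%. The 1.5% and 8% follow from Table 3; the 14.3% and 40% rest on illustrative end points that the article does not supply. The flaw lies in one layer of a two-layer analysis and does not by itself mean that the reported ratio will appear stable. It is worth correcting because the article fixes the rule and the correction is nearly free.

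**What to change.** In Calculating the SROI, replace the common ±10% in the one-way step with each assumption's own plausible range:

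- for judged inputs (the proxies, attribution, displacement, drop-off, and deadweight taken from conversations), the optimistic and pessimistic values that the scenarios already require, set and justified before the ratio is calculated;
- for inputs estimated from data (score changes and the LSAC deadweight for connectedness), the limits of the 95% confidence interval.

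Rank the assumptions by the change in the ratio over those ranges. Keep the best, worse and moderate scenarios for the overall spread. Also report the friendship value at which the ratio equals 1, since that proxy is the largest in Table 3. With equal achieved change and a common factor k for achieved change and deductions, that value is cost/k − 5,450, where 5,450 = 4,200 + 1,250.

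The cost is slightly more analysis work and no new data collection. The reported ranges will be wider and less favourable than those from ±10%.
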